***Sample Size calculation:***

Our power calculations are based on a sample size that can document the minimal clinically important difference (MCID) in VAS knee pain superior to yoga compared to strengthening exercise. Based on the MCID of 15mm in VAS pain [a numerical scale ranging from 0 (no problem) to 100 (maximum problem)], two-sided significance level of 0.05, 90% power and SD of VAS pain change 22.5, we will need a total of 98 participants. Assuming a worse scenario of 20% dropout, we will need 126 participants.

The above sample size will allow us to detect a non-inferiority of yoga with strengthening exercise. Non-inferiority would be declared if the mean change in knee pain (assessed using VAS) in the yoga group was not significantly worse than the mean change in the strengthening exercise group, within a pre-stated margin of non-inferiority ( $\Delta$ ), in this case, set at 10 mm. Overall, 126 participants will give us 80% power to detect the non-inferiority of yoga compared with strengthening exercise.

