***Statistical Analyses:***

The comparisons of pain and other continuous scores will be made using a repeated-measures mixed model with terms of treatment, time, and corresponding baseline values as covariates. The effect of treatment will be evaluated by the intervention by time interaction, and then proceed to the main effects model with only group and time. We will also assess the effects of potential confounders or interaction with treatment by covariates, including age, sex, BMI, disease severity, comorbidities, health status, and use of pain medications. A 2-sided P-value less than 0.05 will be considered to indicate the statistical significance, and the results will be shown as the between-group differences with 95% confidence intervals (95% CIs) of the differences.

We will explore the role of clustering effects in the trial by performing a sensitivity analysis examining the implications of clustering by the instructor by adding an instructor random effect to the mixed-effects model.

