## **Statistical analysis used in final manuscript.**

### **1. Statistical methods (details of primary analyses)**

Analyses were performed using Stata version 18 (Stata Corporation, Inc., College Station, TX, USA) and a two-sided P value of 0.05 was deemed statistically significant.

Normality was assessed by examining the distribution of residuals, and homogeneity of variance was evaluated through visual inspection of plots of residuals versus fitted values.

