3. **Original Protocol:** We stated “the above sample size will allow us to detect a non-inferiority of yoga with strengthening exercise. Non-inferiority would be declared if the mean change in knee pain (assessed using VAS) in the yoga group was not significantly worse than the mean change in the strengthening exercise group, within a pre-stated margin of non-inferiority ( $\Delta$ ), in this case, set at 10 mm”.

**Open access protocol publication:** We stated “the above sample size will allow us to detect a non-inferiority of yoga with strengthening exercise. Non-inferiority would be declared if the mean change in knee pain (assessed using VAS) in the yoga group was not significantly worse than the mean change in the strengthening exercise group, within a pre-stated margin of non-inferiority ( $\Delta$ ), in this case, set at 10 mm”.

**Final Manuscript:** Since our study was powered for non-inferiority and has met the criteria for switching the trial objective from superiority to non-inferiority, as outlined by the European Agency for the Evaluation of Medicinal Products (EMA 2001), we conducted a non-inferiority analysis.

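### The stated 80% power for non-inferiority does not follow from the plan's stated inputs: at its two-sided 0.05 level, power is about 70% with 126 analysed and about 60% after the planned 20% dropout.

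*Combined protocol and SAP*

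**What the plan says.** The trial is sized for superiority. The protocol (Sample Size calculation) starts "Based on the MCID of 15mm in VAS pain", uses "two-sided significance level of 0.05, 90% power and SD of VAS pain change 22.5", and arrives at 98 participants, raised to 126 for 20% dropout. The next paragraph turns to non-inferiority with a 10 mm margin and ends: "Overall, 126 participants will give us 80% power to detect the non-inferiority of yoga compared with strengthening exercise". The SAP (Sample size calculation) repeats this.

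The non-inferiority paragraph gives no significance level, confidence level, assumed true difference or dropout allowance. Elsewhere only one level appears:

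- Protocol, Statistical Analyses: "A 2-sided P-value less than 0.05 will be considered to indicate the statistical significance". Estimates are to be reported with 95% intervals. The SAP's Data analysis section says the same.
- SAP, Statistical methods used in the final manuscript: "a two-sided P value of 0.05 was deemed statistically significant".

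Item 3 of the SAP's summary of changes then explains why a non-inferiority analysis was done: "Since our study was powered for non-inferiority and has met the criteria for switching the trial objective from superiority to non-inferiority".

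**The concern.** The superiority calculation treats 126 as the number recruited and about 98 to 100 as the number analysed. The non-inferiority sentence appears to treat all 126 as analysed. It also appears to use a looser error rate than the two-sided 0.05 stated everywhere else.

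Two things are at stake. First, the power statement was put to use: it is one of the reasons given for changing the trial's objective. Second, it affects how an inconclusive non-inferiority result is read. If the two programs are truly equal, 80% power means a 20% chance of failing to show non-inferiority. At 60% power that chance is 40%.

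The mismatch also leaves the decision rule open. The power figure fits a one-sided 5% error rate (a 90% interval), while the analysis text fixes 95% intervals.

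**Working it through.** **Inputs from the documents.** Margin 10 mm; SD of change 22.5; two-sided 0.05 with 95% intervals; 20% dropout; 126 enrolled (all from the sample size and analysis sections); 1:1 allocation (Randomisation and blinding), so 63 per arm enrolled. After dropout, 126 × 0.8 = 100.8, or about 50 per arm.

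**Assumptions that the documents do not give.** True difference zero; unadjusted comparison of two means with 22.5 as the SD of the analysed quantity.

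**Step 1: the superiority figure.** n per arm = 2 × (1.960 + 1.282)² × (22.5/15)² = 47.3, so 48. With the t distribution, 49 per arm gives 90.4% power, so the stated 98 reproduces. Dropout: 98/0.8 = 122.5, so 123, close to the stated 126.

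**Step 2: the stated 80%.** SE = 22.5 × √(2/63) = 4.01, and 10/4.01 = 2.494.

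- One-sided 0.05: 2.494 − 1.645 = 0.849, power 80.2% (noncentral t: 79.8%). This matches the stated 80%. Solving for n gives 2 × (1.645 + 0.842)² × (22.5/10)² = 62.6, so 63 per arm, or exactly 126.
- One-sided 0.025: 2.494 − 1.960 = 0.534, power 70.3% (t: 69.7%).

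**Step 3: after 20% dropout.** With 50 per arm, SE = 22.5 × √(2/50) = 4.50, and 10/4.50 = 2.222.

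- One-sided 0.025: 2.222 − 1.960 = 0.262, power 60.3% (t: 59.5%).
- One-sided 0.05: 2.222 − 1.645 = 0.577, power 71.8% (t: 71.3%).

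| Analysed | One-sided 0.025 (95% CI) | One-sided 0.05 (90% CI) |
|---|---|---|
| 126 | 70.3% (t 69.7%) | 80.2% (t 79.8%) |
| 100 | 60.3% (t 59.5%) | 71.8% (t 71.3%) |

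**Step 4: size of the gap.** 80% at one-sided 0.025 needs 2 × (1.960 + 0.842)² × (22.5/10)² = 79.5, so 80 per arm: 160 analysed, or 160/0.8 = 200 enrolled. This shows the scale only; it is not a proposal to enrol more.

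**Step 5: sensitivity to the assumptions, at one-sided 0.025.**

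- *True difference.* The yoga advantage needed for 80% power is (1.960 + 0.842) × SE − 10: about 1.2 mm with 126 analysed (SE 4.01) and 2.6 mm with 100 (SE 4.50).
- *Baseline adjustment.* With equal variances and baseline–follow-up correlation r, the adjusted SD is 22.5 × √((1 + r)/2). The values of r are assumed. At r = 0.3 the SD is 18.1 and power is 87% with 126 and 79% with 100. At r = 0.5 the SD is 19.5 and power is 82% and 73%.

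**The case against.** The strongest defence has four parts.

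**The 80% is not an arithmetic slip.** A reader might infer one, but the figure is correct for one-sided 0.05 with all 126 analysed, and the non-inferiority paragraph states no level of its own. This stands as a description of how the number arises. It does not rescue the statement: no one-sided 0.05 is declared anywhere, every stated level is two-sided 0.05, and 80% is missed at either level once the plan's own dropout is applied.

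**The planned analysis may be more powerful than an unadjusted comparison.** The mixed model adjusts for baseline, uses the VAS at weeks 4, 8 and 12, and can use partial data from people who drop out. A small true advantage for yoga, which is the trial's hypothesis, would also help. This stands too. A reader might infer that 80% is out of reach under any analysis, and the documents do not support that. With assumed correlations of 0.3 to 0.5, baseline adjustment exceeds 80% with 126 analysed, though not with 100; a correlation of about 0.25 or less would reach 80% even with 100. But the plan gives no correlation, claims no such gain and states no assumed true difference.

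**The switch does not rest on power alone.** The summary of changes also cites having met criteria for switching, and the 10 mm margin was stated in advance. It would therefore be wrong to infer that the whole basis for the switch falls.

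**Planned power does not decide the result.** Non-inferiority depends on where the confidence interval lies against 10 mm. It would be wrong to infer that low planned power invalidates a positive finding. What remains is the accuracy of the stated ground and the reading of an inconclusive interval.

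**Conclusion.** The concern holds as a misstatement of power. For an unadjusted comparison with SD 22.5, a 10 mm margin and zero true difference, the plan's two-sided 0.05 level gives about 70% power with 126 analysed and about 60% with about 100, against 80% stated. Applying the dropout allowance alone, at the looser one-sided 0.05, still leaves about 71%.

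The zero difference and the unadjusted comparison are assumptions made here, not inputs from the plan, and relaxing either could raise the figures. The faults are an undeclared error rate and an omitted dropout allowance. They matter because the claim that the study was powered for non-inferiority is offered as one reason for changing the objective. The superiority sizing is unaffected.

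**What to change.** The protocol is an approved document and the analyses are done, so make the change as a dated correction rather than by rewriting the approved text.

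1. For the sample size sections of the protocol and the SAP, state: *With a 10 mm margin, SD 22.5, no true difference, an unadjusted comparison and a two-sided 95% confidence interval (one-sided 0.025), power for non-inferiority is about 70% with 126 analysed and about 60% with about 100 analysed after 20% dropout.*
2. State that non-inferiority is judged by the two-sided 95% confidence interval against 10 mm.
3. In item 3 of the SAP's summary of changes, replace the claim that the study was powered for non-inferiority with the pre-stated 10 mm margin and the corrected power, and describe the non-inferiority analysis as secondary to superiority.

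The cost is a few sentences and a less favourable stated power. No extra participants and no new analysis are needed.

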***Statistical Analyses:***

The comparisons of pain and other continuous scores will be made using a repeated-measures mixed model with terms of treatment, time, and corresponding baseline values as covariates. The effect of treatment will be evaluated by the intervention by time interaction, and then proceed to the main effects model with only group and time. We will also assess the effects of potential confounders or interaction with treatment by covariates, including age, sex, BMI, disease severity, comorbidities, health status, and use of pain medications. A 2-sided P-value less than 0.05 will be considered to indicate the statistical significance, and the results will be shown as the between-group differences with 95% confidence intervals (95% CIs) of the differences.

We will explore the role of clustering effects in the trial by performing a sensitivity analysis examining the implications of clustering by the instructor by adding an instructor random effect to the mixed-effects model.

***Cost-effectiveness analysis:***

We will perform the cost-effectiveness analysis (CEA) by measuring the costs and benefits in the *yoga program* group and the *strengthening exercise program* group. Mean differences in total costs and benefits between the *yoga program* and *strengthening exercise program* at 12 weeks and 24 weeks follow-up period will be calculated. Incremental cost-effectiveness ratios (ICERs) will be determined by dividing the difference in total costs by the difference in total benefits for both groups (equation below). We will also conduct the subgroup analysis based on the degree of knee pain at baseline, the adherence to the *yoga program*, gender, socioeconomic status.

**Measurement of costs**

The health questionnaires completed by participants at baseline, 12-weeks, and 24-months will provide data on “health service use”. This data will include visits to GPs, practice nurses, and any other health professionals (e.g. physiotherapists) for the treatment and/or management of knee OA. To estimate total costs, we will assign unit costs for each visit to a health care professional. Unit costs will be obtained from national published sources such as the appropriate Australian Annual Medicare Statistics providing health service unit cost and the Indexation of Medicare Benefits Schedule (48).

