**Outcomes and assessments:**

There will be four study clinic visits (screening, baseline/week 0, week 12, week 24) for objective assessments such as core physical function measures, muscle strength, neuromuscular variables, and functional balance. Pain and function will be assessed at each time point (week 0, 4, 8, 12, 16, 20, and 24) using a 100mm visual analogue scale (VAS) and asked: “On this line, how would you rate your symptoms in the last week”? We will also assess symptoms using the WOMAC scale. We will include other questionnaires on psychological, QoL (AQoL and EQ-5D), as well as adherence to therapy and healthcare utilisation of the treatment for knee OA.

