#### **Other outcomes:**

16. Change in gait characteristics such as step length, double support time, step width, and step time from baseline to week 12 and baseline to 24 weeks.
17. Change in body fat will be assessed using bioelectrical impedance analysis (BIA) (BIA analyser, Quantum II, RJL Systems, Michigan, USA) at baseline, week 12, week 24. We will assess fat-free mass, percentage fat-free mass, fat mass and percentage fat mass.

The health economic measures to be collected at baseline, 12-week, and week 24 include: health service use including visits to GPs, specialist doctors, physiotherapists; medical imaging, procedures, tests and investigations for knee pain; hospital admissions and attendances for knee pain, and community service use for knee pain. We will also collect information on costs for transport and specialised equipment purchased/hired due to knee pain. We will collect information about employment, days absent from work, presenteeism, and sick leave due to knee pain. To assist with cost estimation, we will collect information about participants' concession, health care card & private health insurance status.

In combination with the clinical data, these data will be used to conduct a cost-effectiveness analysis of *yoga program* versus *strengthening exercise program*. We will test that hypothesis that *yoga program* will be cost-effective than the *strengthening exercise program*.

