**Measurement of benefit**

The AQL-8D and EQ-5D-5L will be used to determine HSU for each participant. Mean scores and measures of dispersion will be calculated for both groups. Quality-adjusted life-years (QALYs) will be calculated using two approaches: change from baseline (CfB), and area under the curve (AUC) approach with/without linear regression (49, 50).

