#### Uncertainty and sensitivity analysis

A summary measure of the uncertainty of costs and effects will be presented using cost-effectiveness acceptability curves (CEAC). The CEAC will show a range of probabilities of an intervention being cost-effectiveness at different ceiling thresholds (i.e. a maximum amount that decision-makers are willing to pay for a unit of benefit). To test the robustness of the results, a series of sensitivity analyses will be conducted to explore the variability in estimating cost-effectiveness.

$$ICER = \frac{\text{mean cost yoga program group} - \text{mean cost physical therapy group}}{\text{mean QALY yoga program group} - \text{mean QALY physical therapy group}}$$

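### Incremental cost is planned as an unadjusted difference in mean costs, although baseline service use is collected and regression is already offered for QALYs

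*Combined protocol and SAP*

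**What the plan says.** Protocol, Measurement of costs: "The health questionnaires completed by participants at baseline, 12-weeks, and 24-months will provide data on" health service use. It continues: "To estimate total costs, we will assign unit costs for each visit to a health care professional". No recall period is given, and the section does not say which questionnaires contribute to the total.

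Protocol, Cost-effectiveness analysis: mean differences in total costs and benefits "at 12 weeks and 24 weeks follow-up period will be calculated", and the ICER is obtained by "dividing the difference in total costs by the difference in total benefits for both groups". The equation under Uncertainty and sensitivity analysis writes the numerator as the yoga arm's mean cost minus "mean cost physical therapy group", which is the strengthening arm under another label. No covariate is named for cost.

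Protocol, Measurement of benefit: QALYs may be derived by change from baseline or by an "area under the curve (AUC) approach with/without linear regression".

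On timing, Outcomes and assessments says "There will be four study clinic visits (screening, baseline/week 0, week 12, week 24", and Other outcomes says "The health economic measures to be collected at baseline, 12-week, and week 24 include" the service-use items. The schedule table marks health economics at the same three points: baseline, week 12 and week 24.

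The Statistical Analyses section adjusts pain and other continuous scores for baseline but does not name costs. The SAP section states that no separate plan was written, and its text contains no method for costs.

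**The concern.** Health-care cost usually varies widely between people, and people who used more care before a trial often use more during it. Where that holds, part of the spread in follow-up cost can be predicted from baseline cost. A plain difference in arm means leaves that part in the error.

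The plan is also uneven. It allows regression in the ICER denominator and names none for the numerator, although the baseline value is collected on the same questionnaire. At stake are the width of the interval for incremental cost and the steepness of the acceptability curve. Cost-effectiveness is part of the stated aims, and Other outcomes describes it as a hypothesis to be tested.

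**Working it through.** **Plan's own figure.** There is none to reproduce. The documents give no cost SD, cost difference, power for cost, or correlation between baseline and follow-up cost. The correlation below is therefore an assumption, shown over a range.

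**Inputs from the protocol.** Cost windows ending at baseline, week 12 and week 24 (Other outcomes; schedule table). Allocation 1:1 (Randomisation and blinding). 126 participants and 20% dropout (Sample size calculation), which gives 63 per arm, or about 50 per arm after dropout (126 × 0.8 = 100.8).

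**Set-up.** Let B be cost in the baseline window, F1 cost in the first 12 weeks and F2 cost in the second 12 weeks. Assume equal SD, set to 1, in each window. The 24-week total is F = F1 + F2.

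- Unadjusted variance: Var(F) = 2 + 2r.
- Adjusted variance: Var(F) − Cov(B,F)².
- Exchangeable correlation: Cov(B,F) = 2r, so the adjusted variance is 2 + 2r − 4r².
- AR(1) correlation: Cov(B,F) = r + r², so the adjusted variance is 2 + 2r − (r + r²)².
- The ratio of unadjusted to adjusted standard error is the square root of the variance ratio; sample size cancels.

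| r | Unadjusted variance | Exchangeable: adjusted variance | SE ratio | AR(1): adjusted variance | SE ratio |
|---|---|---|---|---|---|
| 0 | 2.00 | 2.00 | 1.000 | 2.000 | 1.000 |
| 0.3 | 2.60 | 2.24 | 1.077 | 2.448 | 1.031 |
| 0.5 | 3.00 | 2.00 | 1.225 | 2.438 | 1.109 |
| 0.6 | 3.20 | 1.76 | 1.348 | 2.278 | 1.185 |

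At r = 0.3, 0.5 and 0.6 the unadjusted SE is thus about 8%, 22% and 35% larger (exchangeable), or 3%, 11% and 18.5% larger (AR(1)). In variance terms, exchangeable adjustment removes 0.36/2.60 = 14%, 1.00/3.00 = 33% and 1.44/3.20 = 45%.

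**12-week comparison.** Only F1 counts, so the ratio is 1/√(1 − r²) under either structure: 1.05, 1.15 and 1.25 at r = 0.3, 0.5 and 0.6.

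**Chance imbalance.** The SE of the baseline difference between arms is √(2/63) = 0.178 SD, a 95% range of about ±0.35 SD. With 50 per arm it is √(2/50) = 0.20 SD, or ±0.39 SD. At r = 0.5 and exchangeable correlation, the slope of F on B is 2 × 0.5 = 1. An imbalance of 0.35 SD then moves the unadjusted 24-week cost difference by 0.35 of a window SD. The unadjusted SE is √3 × 0.178 = 0.31, so the shift is about 1.1 standard errors. Under AR(1) the slope is 0.75 and the shift is 0.75 × 0.35 = 0.26, about 0.85 standard errors.

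**The case against.** The best defence is that nothing here is wrong in expectation. Under 1:1 randomisation the unadjusted difference is unbiased, and adjustment is an efficiency choice. That stands, so the point concerns precision only.

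It can also be said that the ICER equation is a generic definition. It writes QALYs as plain arm means too, yet regression is expressly allowed for them, so the equation does not forbid adjusting costs. That stands as well. The accurate statement is that baseline-cost adjustment is not pre-specified. The unspecified series of sensitivity analyses does not supply it.

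The gain may be modest. Correlation may decay over time. The exclusion criteria remove people with recent knee surgery, recent injections or a treated knee injury, who may account for much of the high prior use. Unstated recall periods also make equal SDs uncertain. All of this is fair, and it is why the range starts at zero.

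Two stronger readings are tempting but unsupported:

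- **Baseline visits are added into total cost.** Measurement of costs lists baseline as a data source without saying its visits are summed. The Cost-effectiveness analysis section ties totals to the 12- and 24-week follow-up period, and the secondary outcome of change in resource use gives the baseline questionnaire another purpose.
- **Costs over 24 months are set against QALYs over 24 weeks.** No 24-month questionnaire is scheduled. Every other statement of the health-economic time points says week 24, and the timeline places recruitment in 2021 and the final 24-week visits in 2022. The phrase reads as a wording slip, and no such data would exist to analyse.

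**Conclusion.** The concern holds as a missed gain in precision in a secondary analysis. The plan estimates incremental cost without adjusting for a baseline value that it collects. For an assumed between-window correlation of 0 to 0.6, the unadjusted standard error at 24 weeks is 0% to 35% larger than the adjusted one (exchangeable) or 0% to about 18.5% larger (AR(1)). These figures assume equal SDs across windows and a linear adjustment, and they ignore the one degree of freedom spent. If baseline cost does not predict later cost, nothing is gained.

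There is no expected bias and no effect on the pain result. The 24-month time point and the silence on which windows enter the total are matters of clarification; neither shows that a wrong total will be computed.

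**What to change.** Pre-specify incremental cost as the arm coefficient from a regression of post-randomisation cost on arm and baseline-window cost, fitted separately for the 12-week and 24-week totals. Allow for skewed costs, for example by bootstrapping participants, with the cost and QALY models refitted in each resample so that their correlation is kept. Use the adjusted estimate in the ICER and the acceptability curve, and keep raw mean differences as descriptive.

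In the same edit:

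- reconcile the 24-month time point in Measurement of costs with the week-24 schedule given elsewhere;
- state the recall period of each questionnaire, and that total cost counts post-randomisation use only;
- say how missing baseline cost is handled, for example by single imputation from baseline data without reference to arm, so that nobody is dropped.

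The cost is some wording, one covariate and a bootstrap routine; no new data are needed. The downsides are the handling of missing baseline cost and a gain that may prove small. The summary of protocol changes says the health-economic analysis is still under way and will be published separately, so the change can still be made. It should be dated and reported as added after the protocol was approved.

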### **Treatments:**

Overall, 126 eligible participants will be randomly allocated to a 24-week group-based *yoga program* or *strengthening exercise program* (each with two 1-hour group-based sessions and one 1 hour home based session per week). Group sessions will be led by physiotherapist/exercise physiologists/yoga teachers for the first 12 weeks. Trainers will lead a group of approximately 10 participants. Participants will be instructed to continue their *yoga* or *strengthening exercise* at home for another 12 weeks. Using REDCap, weekly email follow-up will be done with the participants to confirm the compliance to the home-based program, and video instructions will be given to each participant to support the home-based program.

An evidence-based *yoga program* designed by a yoga expert and researcher - [name] from the Maryland University of Integrative Health, USA will be delivered by yoga

teachers. Each yoga class will begin with a breathing exercise (*pranayama*) and chanting (10min), warm-up, and moving sequences (*asanas*, 40 min). Classes will end with deep relaxation (*savasana*) and meditation (10 min). Classes will include an application of yoga philosophy and replace negative thoughts with positive ones (*pratipaksa bhavanam*). Details about interventions are in the appendix.

The strengthening exercise therapy regimen will be designed by [name] as a group-based progressive strengthening exercise program based on those used in past clinical trials and shown to be effective. Details about interventions are in the appendix.

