**Health Economics Outcomes (secondary outcomes):**

We will assess health state utility (HSU) values, resource utilisation, and costs throughout the study. Health-related quality of life (HRQoL) and utility will be assessed using the Assessment of Quality of Life (AQoL-8D) and the EuroQol 5 dimensions (EQ-5D-5L) instruments. The health economic outcomes to be collected as the secondary outcome will include:

12. Change in concomitant medications (assessed using self-reported medication history questionnaire) from baseline to 12 and baseline to 24 weeks and associated costs.

13. Self-reported adherence to the intervention and comparator program from baseline to 12 and baseline to 24 weeks assessed using online logbook and defined as the percentage of prescribed session undertaken.
14. Change in QoL (assessed by AQoL-8D and EQ-5D-5L) from baseline to week 12 and baseline to 24 weeks.
15. Change in health resource utilisation (assessed using a self-reported questionnaire) at 12 and 24 weeks.

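### The total-cost rule prices only health-professional visits and omits programme delivery, and the yoga-adherence subgroup has no randomised comparator

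*Combined protocol and SAP*

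**What the plan says.** **The costing rule.** The protocol's Measurement of costs section takes its inputs from participant questionnaires: "This data will include visits to GPs, practice nurses, and any other health professionals (e.g. physiotherapists) for the treatment and/or management of knee OA". It then gives the rule: "To estimate total costs, we will assign unit costs for each visit to a health care professional". On prices it says: "Unit costs will be obtained from national published sources such as the appropriate Australian Annual Medicare Statistics". The SAP text carries no costing rule of its own.

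**What else is collected.** Health Economics Outcomes lists change in concomitant medications "from baseline to 12 and baseline to 24 weeks and associated costs". Other outcomes adds imaging, procedures and tests, "hospital admissions and attendances for knee pain, and community service use for knee pain", transport and equipment costs, and absence and presenteeism. The same section says these data will go into the cost-effectiveness analysis and sets up a test of whether yoga is the cost-effective option. The schedule of assessments includes a medication cost diary, days off work, and transport and equipment costs.

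**The programmes.** Under Treatments, each arm has two one-hour group sessions and one home hour a week, in groups of about 10. On staffing it says: "Group sessions will be led by physiotherapist/exercise physiologists/yoga teachers for the first 12 weeks".

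**Subgroups and QALYs.** The Cost-effectiveness analysis section says: "We will also conduct the subgroup analysis based on the degree of knee pain at baseline, the adherence to the" yoga programme, gender and socioeconomic status. Measurement of benefit computes QALYs from two instruments by "change from baseline (CfB), and area under the curve (AUC) approach with/without linear regression", and names no base case.

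**The concern.** The ICER is meant to compare two programmes, and running them uses resources: leader time, rooms, mats and bands, and videos. A participant questionnaire about visits for knee OA will not capture those costs, and Medicare statistics are not an evident source of prices for them. If the rule is followed as written, the totals contain the downstream care but not the interventions. Any between-arm difference in delivery cost then drops out of the numerator.

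The cost scope is also unsettled. One section prices visits only, another sends a much wider set of items to the same analysis, and no perspective (health system or societal) is stated. Whether medication, hospital care or lost work counts could be decided after the results are known.

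The adherence subgroup is a separate fault. Degree of pain at baseline, gender and socioeconomic status can define the same kind of patient in both arms. Adherence to yoga cannot: it is observed only after allocation, and no strengthening participant has a value for it.

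**Working it through.** The documents state no cost, QALY or ICER figure, so there is nothing to reproduce. The check has three parts.

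**1. Cost scope, section against section**

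| Item | Collected or used in the trial | In the total-cost rule |
|---|---|---|
| Visits to health professionals | Yes | Yes |
| Medication | Yes (Health Economics Outcomes; schedule) | No |
| Imaging, tests, hospital, community services | Yes (Other outcomes) | No |
| Transport, equipment, work loss | Yes (Other outcomes; schedule) | No |
| Programme delivery (leader, venue, mats, bands, videos) | Used, but no section says it is measured or priced | No |

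**2. Size of the delivery-cost omission (illustration)**

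Inputs from Treatments: 2 led hours a week × 12 weeks = 24 led hours per group; about 10 people per group in both arms.

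Assumed inputs, absent from the documents: leader rates of $60–150 per hour; a between-arm rate difference of $10–100 per hour; a QALY difference of 0.005–0.02. Over 24 weeks (24/52 = 0.46 years), that QALY range corresponds to a mean utility difference of about 0.005/0.46 = 0.011 to 0.02/0.46 = 0.043.

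- Gross delivery cost per participant = 24 × rate / 10. At $60 this is $144 and at $150 it is $360.
- Increment per participant = 24 × (rate in yoga / group size in yoga − rate in strengthening / group size in strengthening).
- ICER shift = increment / QALY difference.

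With groups of 10 in both arms:

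| Rate difference ($/h) | Increment per participant | Shift at 0.005 QALY | Shift at 0.01 QALY | Shift at 0.02 QALY |
|---|---|---|---|---|
| 0 | $0 | $0 | $0 | $0 |
| 10 | $24 | $4,800 | $2,400 | $1,200 |
| 50 | $120 | $24,000 | $12,000 | $6,000 |
| 100 | $240 | $48,000 | $24,000 | $12,000 |

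Unequal attendance can have the same effect at equal rates. Groups of 8 against 10 at $100 per hour give 24 × 100 × (1/8 − 1/10) = $60. Groups of 6 against 10 at $150 give 24 × 150 × (1/6 − 1/10) = $240.

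**3. Adherence subgroup and QALY methods**

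Health Economics Outcomes logs adherence in both arms, after randomisation, as the percentage of prescribed sessions done. The subgroup is named for yoga only. Splitting the yoga arm on this variable leaves no corresponding split of the strengthening arm, so the ICER within a stratum is not protected by randomisation.

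For QALYs, if the regression option applies to AUC only, there are 2 instruments × 3 methods = 6 estimates at each of 2 time points, or 12 possible ICERs with none designated as primary.

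**The case against.** The strongest reply on costs is that an ICER depends only on the difference between arms. Both arms have the same schedule, the same planned group size and video support, and the Safety section describes mats and bands without distinguishing arms. Much of the delivery cost may therefore cancel. This stands, and it rules out two readings. A reader might infer that the ICERs would be wrong as planned; the documents give no rates, and the error is zero if delivery costs are equal. A reader might also take the $144–360 gross cost as the size of the error; it is incurred in both arms and is not a difference.

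Cancellation is nevertheless an assumption that the plan neither states nor supports. Yoga classes are given by yoga teachers, while the list of leaders also includes physiotherapists and exercise physiologists. The SAP summary of changes reports that one instructor ran more than 80% of the yoga classes and another more than 80% of the strengthening classes. The body text does not say who leads strengthening, so a difference in profession is likely but not documented.

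A second reply is that the wider data will be used, because Other outcomes says so. That is fair: it would be too strong to say the whole plan prices visits only. The fault is a conflict between sections, and it does not supply the missing delivery costs.

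On adherence, a reader might infer that good yoga adherers will be set against all strengthening participants, to yoga's advantage. The protocol does not specify that comparison, and adherence is recorded in both arms. The objection to the subgroup as named remains.

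**Conclusion.** The point holds in limited form. The total-cost rule is incomplete, it conflicts with the rest of the protocol, and it omits delivery of the two programmes being compared. The main ICER is biased if delivery cost per participant differs between arms. Under the assumed inputs the shift runs from $0 (equal costs) to about $1,200–48,000 per QALY for a rate difference of $10–100 per hour, and its direction is unknown. That the omission would reverse the sign of the incremental cost is not something the documents can show.

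The adherence problem affects only that subgroup's ICER. The missing QALY base case is a lesser pre-specification gap, since baseline-adjusted AUC is already among the planned methods. The primary pain comparison is untouched. The economic analysis is secondary, and the Summary of protocol changes says it is still in progress for separate publication, so correction should still be possible.

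**What to change.** - **Measurement of costs:** state the costing perspective. Define total cost as programme delivery cost per participant by arm (leader time, venue, equipment, videos) plus health service use, medication and hospital care. Add transport, equipment bought or hired, and productivity in a societal analysis. Make the list agree with Health Economics Outcomes, Other outcomes and the schedule.
- **Cost-effectiveness analysis:** delete the yoga-adherence subgroup. Alternatively, replace it with a complier-average analysis that keeps the randomised comparison, uses the adherence logged in both arms, and states its definition of adherence and its assumptions.
- **Measurement of benefit (preferable):** name AUC QALYs with regression adjustment for baseline utility as the base case, and the other calculations as sensitivity analyses.

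The cost is rewording and a small amount of extra work to cost programme delivery. No new patient data are needed.
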